### Interventions

#### CIMT

Once patients are randomly assigned to respective groups, patient-specific rehabilitation is delivered under supervision of the study principal investigator and physical therapist (EP) in an outpatient setting at the Cleveland Clinic main campus. All patients receive CIMT for 30 minutes, twice a day, 3 days a week for 5 weeks. It includes massed (intensive) functional exercises for the paretic upper limb guided by the principle of shaping
[47], which involves a graded, regimented, feedback-driven approach to achieving impairment- and patient-specific goals. Tasks focus upon transfer to real-world activities, including activities like grooming, making a telephone call, et cetera. The protocol of CIMT discussed here differs slightly from the modified version of the program that is generally employed
[46]. Instead of one 30-minute session, we deliver two 30-minute sessions; rather than 10 weeks, we deliver CIMT for 5 weeks, at the same frequency, that is, three times a week. We have incorporated this frequency and length to improve compliance, as patients are required to visit the outpatient clinic 15 times over 5 weeks rather than 30 times over 10 weeks. Patients’ use of the non-paretic upper limb is restrained by placing it in a mitt, which they are asked to maintain for 2 hrs every weekday during peak times of activity, instead of 5 hrs.

#### tDCS

The tDCS of anodal polarity is delivered to PMC in the stroke-affected hemisphere to potentially raise its activity
[49]: it is delivered using a constant current battery-driven (9-V) stimulator (Soterix, NY, New York, USA) connected to conductive rubber electrodes (5 × 7 cm^2^) placed in saline-soaked sponges
[61]. The anodal electrode is placed on the scalp site corresponding to PMC
[34,61], guided by MRI-based stereotaxy. Specifically, the center of the anode is 3 cm anterior to the locus in the stroke-affected hemisphere that evokes the best and most consistent responses with TMS in a muscle of the paretic hand
[61]. The reference (cathodal) electrode is placed above the contralateral orbit. Electrodes are secured using Velcro bands. Direct current is delivered at a dose of 1 mA during rehabilitation in patients in the tDCS plus CIMT group. For patients in the sham tDCS plus CIMT group, the 1 mA current is delivered transiently (30 to 60 seconds) at outset, and then slowly turned off after habituation. For all patients, the current is ramped up slowly at the onset of intervention to minimize excessive tingling and maintain blinding. This is a valid method for placebo as patients receiving tDCS become habituated to its sensation within a short time
[62].

### Blinding

Patients and investigators assessing outcomes are blinded to the group assignment. Double blinding is intended to minimize bias that could emerge from participants’ perceptions of treatment and therapeutic confusion or observer bias within the investigative team about the benefits of the approach. To quantify the success of double blinding, we ask patients at the end of the study whether they believed they received tDCS or sham tDCS, or whether they did not have reason to believe one way or another. A similar questionnaire is completed with the investigators who assess outcomes.

### Safety

A report on side effects is completed at every visit. At every treatment visit, the report documents whether or not subjects experienced side effects related to tDCS, such as tingling, headache, itching, fatigue, pain and problems concentrating. On days of testing with TMS, the report also documents whether subjects experienced side effects related to TMS, such as seizure, loss of consciousness or hearing difficulties. Transient side effects are documented separately from serious events that are categorized as related or unrelated to interventions. Serious adverse events include those that may require inpatient hospitalization. Adverse event reporting follows guidelines set by the local Institutional Review Board. To ensure safety in case of seizure or any unrelated serious medical issues, provisions include an on-call medical response team and clinical research nursing support that work closely with the physician on the study (AM).

### Attrition

We are defining attrition as a lapse in treatment >1 week, inability to complete post-test or follow up, or exclusion or withdrawal in the case of a serious adverse event or development of a condition that is a contraindication to participation in the study.

### Sample size estimation

The sample size has been estimated based on previous studies that have paired invasive or noninvasive stimulation with rehabilitation
[8,9,12,17,31]. Because UEFM has been most commonly investigated across the majority of studies, we used the effect sizes calculated across these studies to generate several permutations of sample size and the corresponding extent of change in the UEFM score (Figure 
2) to estimate power. Using a method of simulations
[63] where 500 simulations were performed, we estimated sample sizes that would generate significant differences upon the UEFM based on a mixed-effects model. From this method, we have found that a sample size of 10 per group would yield 83% power (95% CI 79.41 to 86.19%) to detect differences between groups (PMC tDCS plus CIMT sham tDCS plus CIMT group), 99.6% power to note differences across time (95% CI 98.56 to 99.95%) and 97% power (95% CI 95.35 to 99.46%) to observe a group X time interaction (Figure 
2).

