### Gaps in the theoretical basis and variability in experimental design

Studies have invariably targeted M1 in the stroke-affected hemisphere
[8-10,15]. Given that M1 and its output pathways are spared only in few patients with focal lesions
[20,21], targeting M1 may be ineffective across most. It is thus important to deviate from the classical strategy of stimulating M1 while still realizing that effectiveness may vary depending upon who is enrolled. Well recovered patients demonstrate promise of additive stimulation
[14,22], but disappointing results are observed in patients with severe impairments
[16,18]. The obvious theoretical questions remain - are the effects of adjuvant cortical stimulation favorable for some versus others, and why?

The clinical utility of paired stimulation in rehabilitation is also marred by variability in design. The paired approach has been compared to either rehabilitation alone in unblinded trials
[8-10] or to unconvincing sham stimulation
[16,23] or to no control conditions at all
[24,25]. Approaches of stimulation are extremely variable too, with little information about why one method may have greater utility than another. Invasive techniques (intracranial stimulation of residual M1) carry serious postsurgical risks
[8], but even noninvasive methods (delivered from over the scalp and skull), such as repetitive transcranial magnetic stimulation, rTMS, may induce acute seizures
[26]. Plus, rTMS is non-portable, and impractical to apply in chronic rehabilitation
[27], unlike invasive stimulation
[8-10]. Modes of stimulation are distinct too, with some facilitating activity of stroke-affected hemisphere, and others downregulating that of the unaffected
[28].

Rehabilitation strategies are inconsistent; some groups employ laboratory-based training paradigms
[13,14,22,29], whereas others use standard
[8-10,16,17,23-25,30] or newer methods of rehabilitation
[12,18,31]. It is critical to understand that the type of training that is combined with stimulation determines how generalizable the benefits would be. Improvements are specific for tasks that are strategically paired with stimulation
[7,29,32], thus, choosing a rehabilitative intervention/paradigm that is applicable across most activities of daily living would indeed be more meaningful. Additionally, duration is important because singular sessions of paired stimulation and training tend to be positive

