### Randomization

We are using randomization blocks in sizes of four, where two patients in a block are assigned to PMC tDCS plus CIMT and the other two to the sham tDCS plus CIMT group. Such block randomization prevents the possibility that several patients in a row would get randomized to tDCS or sham tDCS groups in the early part of the study. The order of patients in blocks is random, generated using an online tool. Allocations are concealed in an opaque envelope and hidden in a locked cabinet with restricted access; they are opened by an investigator not involved in data collection or analysis before the first day of treatment.

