**Figure 2 F2:**
[figure not shown]
**Power analysis: power was determined by simulation.** Lower and upper lines define exactly the 95% CI for power, calculated based on the binomial distribution. N is the total sample size. The analysis was performed at a 0.05 significance level considering 2 × 2 factorial analysis of variance (ANOVA) (tDCS plus CIMT and sham tDCS plus CIMT from pretest to post-test). Power has been estimated here for an interaction term (A *C).

Although the estimated sample size appears small, it is commensurate with the pilot exploratory nature of our study. Pilot studies involving brain stimulation generally use smaller sample sizes compared to rehabilitation trials
[28] because contraindications to brain stimulation/imaging are constraining. Still, we anticipate having adequate statistical power based on prior evidence where despite enrolling a total of 14 to 30 subjects, several studies report significant benefit of adjunctive stimulation
[8,30,44]. Additionally, use of a repeated-measures design further provides greater power. Studying neural mechanisms with fMRI and tractography in limited sample sizes is challenging. Given the exploratory nature of our pilot study, we would be able to highlight elemental neural mechanisms of recovery. Previously, in a three-group, randomized controlled study design with a small sample of 20, we deciphered correlates of fMRI
[37]. Recently too, Stagg *et al*.
[64] show differences in fMRI activation across varying types of tDCS interventions in 11 patients with stroke. Without overemphasizing the importance of small pilot studies, we stress instead the significance of large-scale studies in generating clear evidence of efficacy. Our current pilot exploratory study is a step in that direction as it would offer estimates of effect size related to PMC tDCS and neural markers that can serve as entry criteria.

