### Statistical and data analyses

Feasibility: analysis of feasibility includes investigating the rigor of experimental blinding and determining compliance with the 5-week outpatient rehabilitation program. A chi-square analysis will determine whether patients in one group versus another estimate their group assignment correctly. Investigators also complete a similar questionnaire at the end of the study. While patient responses will indicate the rigor of the blinding procedures, responses from investigators will ensure investigator equipoise, preventing observer bias. Attrition or missing data will be analyzed using a strategy known as multiple imputations
[65], where each missing value is replaced with a set of plausible values that represent the uncertainty about the true value. The multiple imputed data sets are analyzed using standard procedures used for complete datasets and by combining results from these analyses. The method of multiple imputations does not attempt to estimate each missing value through simulated values, but rather represents a random sample of missing values. This process results in valid statistical inferences that properly reflect the uncertainty due to missing values.

Safety: the incidence of adverse events in each group will be computed as a proportion of individuals in each group who experienced side effects. We will be using the Fisher exact test to contrast the incidence of side effects between both groups.

Efficacy and markers of recovery: our primary endpoint of efficacy is the UEFM. Secondary outcomes include nine-hole peg test, Action Research arm test, motor activity log, finger abduction strength and the modified Ashworth scale of spasticity. A general linear mixed-model approach will be followed to analyze functional outcomes across three levels of time (pre, post, and follow-up). Significant two-way interaction, whenever present, will be explored using the Tukey honestly significant difference (HSD) test. Non-parametric tests will be used if the distribution is not normal.

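### Only the group-by-time power concerns the treatment effect; the 83% and 99.6% beside it do not, and the interval printed for the interaction cannot come from 500 simulations

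*Protocol article*

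**What the plan says.** Under Sample size estimation, the protocol article reports powers from 500 simulated trials of the upper extremity Fugl-Meyer score (UEFM) under a mixed-effects model. It says that "a sample size of 10 per group would yield 83% power (95% CI 79.41 to 86.19%) to detect differences between groups". It then gives 99.6% (98.56 to 99.95%) for differences across time, and "97% power (95% CI 95.35 to 99.46%) to observe a group X time interaction".

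The Figure 2 legend describes the power model as "considering 2 × 2 factorial analysis of variance (ANOVA) (tDCS plus CIMT and sham tDCS plus CIMT from pretest to post-test"), at the 0.05 level. It says that the limits are exact and binomial, and that the figure shows power for the interaction. The text after the legend says the authors expect their power to be adequate, by reference to earlier studies of 14 to 30 subjects.

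Under Statistical and data analyses, a general linear mixed model will "analyze functional outcomes across three levels of time (pre, post, and follow-up"), and a significant two-way interaction will be explored further. The Abstract describes the analysis as one of change from before to after the intervention.

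**The concern.** Three powers stand side by side as support for 20 patients, and the first is worded as power to see a difference between the groups. A reader will naturally take 83% as the chance of detecting a benefit of stimulation. In a model with a pretest and a post-test, however, the group term is the arm difference averaged over both visits. Randomisation makes the expected pretest difference zero, so this term dilutes the treatment effect. The time term pools the arms and says nothing about stimulation against sham. The interaction, which is the arm difference in pre-to-post UEFM change, is the term that carries efficacy.

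The interval for that term also looks wrong. It is lopsided around 97% in a way that the other two intervals do not lead one to expect.

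What is at stake is how the sample size is understood. If the power is read as adequate without the size of effect attached, readers may expect more of 20 patients than the design can give.

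**Working it through.** **Inputs from the article.** 10 per arm (Sample size estimation), 1:1 in blocks of four (Randomization), significance level 0.05, two visits and exact binomial limits (Figure 2 legend), and 500 simulations. Two-sided testing is assumed, since the article does not state it. No UEFM difference, SD or correlation appears in the readable text. Figure 2 is not shown and may contain some of these.

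**1. Intervals.** Exact (Clopper-Pearson) 95% limits for x successes out of 500:

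| Count | Power | Exact limits | Printed |
|---|---|---|---|
| 415 | 83.0% | 79.41 to 86.19 | 79.41 to 86.19 (group) |
| 498 | 99.6% | 98.56 to 99.95 | 98.56 to 99.95 (time) |
| 485 | 97.0% | 95.10 to 98.31 | – |
| 486 | 97.2% | 95.35 to 98.46 | 95.35 to 99.46 (interaction) |
| 493 | 98.6% | 97.14 to 99.44 | – |
| 494 | 98.8% | 97.41 to 99.56 | – |

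The group and time intervals reproduce to the last digit. A search over all counts finds none that gives 95.35 to 99.46. The lower limit belongs to 486/500, whose upper limit is 98.46, so the printed value differs by one digit.

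**2. Which term measures the treatment effect.** Let D be the arm difference at post-test, with equal expected baselines, a common SD σ at both visits, and pre-post correlation ρ.

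- Interaction: the difference in mean change is D, and the SD of change is σ√(2(1−ρ)). Hence d_int = D / (σ√(2(1−ρ))).
- Group: the difference in the two-visit mean is D/2, and its SD is σ√((1+ρ)/2). Hence d_grp = D / (σ√(2(1+ρ))).

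Thus d_grp = d_int·√((1−ρ)/(1+ρ)): group power depends on ρ even when interaction power is fixed. Holding the interaction at 97% (d_int = 1.82), group power is 60% at ρ = 0.5, 25% at ρ = 0.8 and 14% at ρ = 0.9 (illustrative values of ρ).

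**3. Size of effect behind the power.** Noncentral t, 18 df, noncentrality d√(10/2):

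- 97% power needs d_int = 1.82 SD of change (1.83 for 97.2%).
- 80% power needs 1.32 SD of change.
- The 95% CI half-width is 2.101 × √(2/10) = 0.94 SD of change.

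**4. What 83% and 97% imply together.** 83% needs d_grp = 1.378 and 97% needs d_int = 1.818. The squared ratio is (1.818/1.378)² = 1.74, so ρ = (1.74 − 1)/(1.74 + 1) = 0.27. Then D = 1.818 × √(2 × 0.73) ≈ 2.2 SD of a single UEFM score. Over the printed limits, with 98.46 as the interaction's upper limit, D runs from 2.1 to 2.3.

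**5. Secondary checks.** In simulations with three visits under compound symmetry, interaction power was about 99% if the effect is fully kept or fully lost at follow-up, and about 95% if half is kept. With 9 or 8 analysed per arm in the two-visit model, the 97% becomes 95% or 92%.

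**The case against.** The strongest reply is that the article does give the right figure. It reports power for group by time, the Figure 2 legend says the figure powers the interaction, the analysis section follows up that interaction, and the Abstract speaks of pre-to-post change. Nothing labels the 83% or the 99.6% as the efficacy test. This stands, and a reader who infers that none of the powers belongs to the planned efficacy analysis goes too far. It does not excuse offering the other two as support for the sample size.

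The interval is very probably a misprint of 98.46, and it changes neither the power nor the number of patients. That also stands.

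The article calls itself a pilot and exploratory study, concedes that its sample may be limited, and leaves clear evidence of efficacy to large studies. It therefore does not invite readers to take a null result as evidence against premotor stimulation. It does still claim adequate power.

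Other stronger readings are not supported:

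- **That the plan assumed 2.2 SD.** This is an inference that needs equal baselines and equal variances. If the simulation carried a baseline difference of 0.28 SD at ρ = 0.5, the same two powers would follow from an effect of 1.8 SD.
- **That the assumed effect is undisclosed.** The text says Figure 2 shows the extent of UEFM change.
- **That power fails for a 3.5-point difference.** The article uses 3.5 points as a within-patient responder criterion, not as an arm difference, and gives no SD of change.
- **That the source effects are inflated by placebo response.** The Background does say of a set that includes two of the five source studies that "The paired approach has been compared to either rehabilitation alone in unblinded trials". The size of any placebo share, and the weight of those two studies, depend on sources not at hand.
- **That the third visit or attrition undermines the 97%.** Both are real differences from the power model, but they move it little.

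**Conclusion.** The point holds in a limited form. The 83% and 99.6% are not power for the treatment effect; the 97% is. Its printed interval is certainly wrong, with an upper limit about one percentage point too high. With 10 per arm, adequate power means a difference of about 1.3 SD of change at 80% and about 1.8 SD at 97%, with a confidence interval of about ±0.94 SD. These figures rest on a two-sided 0.05 test of pre-post change with all 20 patients analysed. The joint figures (correlation about 0.27, post-test difference about 2.2 SD of a single score) are conditional on equal expected baselines and variances. They should be confirmed against the simulation's inputs rather than reported as the plan's assumption. The severity is minor to moderate, since neither the number of patients nor the analysis has to change.

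**What to change.** In Sample size estimation:

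1. Remove the group and time powers as justification for the sample size.
2. Name the pre-to-post group-by-time contrast in UEFM as the powered efficacy test. Report power for that contrast only, with the assumed effect in SD of change.
3. Check the simulation count and print either 97.2% (95.35 to 98.46) or 97.0% (95.10 to 98.31).
4. Replace the claim of adequate power with the detectable difference (about 1.3 SD of change at 80% power) and the expected CI half-width (about 0.94 SD).

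A sentence noting that the power model has two visits, the analysis three, and that all 20 patients are assumed analysed would settle the secondary points.

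The cost is one rewritten paragraph and a less favourable power statement. No extra patients are needed.

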**Figure 2 F2:**
[figure not shown]
**Power analysis: power was determined by simulation.** Lower and upper lines define exactly the 95% CI for power, calculated based on the binomial distribution. N is the total sample size. The analysis was performed at a 0.05 significance level considering 2 × 2 factorial analysis of variance (ANOVA) (tDCS plus CIMT and sham tDCS plus CIMT from pretest to post-test). Power has been estimated here for an interaction term (A *C).

Although the estimated sample size appears small, it is commensurate with the pilot exploratory nature of our study. Pilot studies involving brain stimulation generally use smaller sample sizes compared to rehabilitation trials
[28] because contraindications to brain stimulation/imaging are constraining. Still, we anticipate having adequate statistical power based on prior evidence where despite enrolling a total of 14 to 30 subjects, several studies report significant benefit of adjunctive stimulation
[8,30,44]. Additionally, use of a repeated-measures design further provides greater power. Studying neural mechanisms with fMRI and tractography in limited sample sizes is challenging. Given the exploratory nature of our pilot study, we would be able to highlight elemental neural mechanisms of recovery. Previously, in a three-group, randomized controlled study design with a small sample of 20, we deciphered correlates of fMRI
[37]. Recently too, Stagg *et al*.
[64] show differences in fMRI activation across varying types of tDCS interventions in 11 patients with stroke. Without overemphasizing the importance of small pilot studies, we stress instead the significance of large-scale studies in generating clear evidence of efficacy. Our current pilot exploratory study is a step in that direction as it would offer estimates of effect size related to PMC tDCS and neural markers that can serve as entry criteria.

### Statistical and data analyses

Feasibility: analysis of feasibility includes investigating the rigor of experimental blinding and determining compliance with the 5-week outpatient rehabilitation program. A chi-square analysis will determine whether patients in one group versus another estimate their group assignment correctly. Investigators also complete a similar questionnaire at the end of the study. While patient responses will indicate the rigor of the blinding procedures, responses from investigators will ensure investigator equipoise, preventing observer bias. Attrition or missing data will be analyzed using a strategy known as multiple imputations
[65], where each missing value is replaced with a set of plausible values that represent the uncertainty about the true value. The multiple imputed data sets are analyzed using standard procedures used for complete datasets and by combining results from these analyses. The method of multiple imputations does not attempt to estimate each missing value through simulated values, but rather represents a random sample of missing values. This process results in valid statistical inferences that properly reflect the uncertainty due to missing values.

Safety: the incidence of adverse events in each group will be computed as a proportion of individuals in each group who experienced side effects. We will be using the Fisher exact test to contrast the incidence of side effects between both groups.

Efficacy and markers of recovery: our primary endpoint of efficacy is the UEFM. Secondary outcomes include nine-hole peg test, Action Research arm test, motor activity log, finger abduction strength and the modified Ashworth scale of spasticity. A general linear mixed-model approach will be followed to analyze functional outcomes across three levels of time (pre, post, and follow-up). Significant two-way interaction, whenever present, will be explored using the Tukey honestly significant difference (HSD) test. Non-parametric tests will be used if the distribution is not normal.

To assess neural substrates of recovery, both groups will be compared for change in inter-hemispheric balance (fMRI), fc and transcallosal inhibition and corticospinal conduction (TMS) from pretest to post-test. To understand whether effects of interventions vary across patients and factors explaining such variance, an ideal method would have involved identifying clinical, pathologic and neural factors that would predict the change in UEFM. However, since the statistical power of the study may be inadequate to pursue this analysis, we will follow an alternative method. Patients who achieve ≥3.5 gain in the UEFM score (criterion of clinical improvement defined in a previous clinical trial of invasive cortical stimulation)
[8] after 5 weeks of the intervention would be called responders. We will investigate whether the proportion of responders versus nonresponders includes a greater majority of patients from the tDCS group (Chi-square analysis). More importantly, we will compare clinical, pathologic and neural indicators between responders and nonresponders (independent samples *t*-test). These will include: baseline UEFM, location of disease (Oxford Stroke classification: total anterior circulation or partial anterior circulation or lacunar strokes)
[66], residual function and integrity of corticospinal tracts on the stroke-affected side measured with TMS and diffusion tensor imaging respectively.

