**Methods/Design:**

In a randomized, sham-controlled, double-blinded pilot clinical study, patients with chronic stroke (n = 20) are assigned to receive transcranial direct current stimulation delivered to the premotor cortex or sham during rehabilitation of the paretic arm/hand. Patients receive the designated intervention for 30 min, twice a day for 3 days a week for 5 weeks. We assess hand function and patients’ reports of use of paretic hand. A general linear mixed methods model will analyze changes from pre- to post-intervention. Responders and non-responders will be compared upon baseline level of function, and neural substrates, including function and integrity of output tracts, bi-hemispheric balance, and lesion profile. Incidence of adverse events will be compared using Fisher’s Exact test, while rigor of blinding will be assessed with Chi-square analysis to ascertain feasibility.

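### As worded, the patient blinding test compares correct-guess rates between arms: it cannot detect unblinding that is equal in both arms, and it can flag good blinding when most patients guess the same treatment

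*Protocol article*

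**What the plan says.** The Abstract (Methods/Design) names the test and its purpose: "rigor of blinding will be assessed with Chi-square analysis to ascertain feasibility". It does not say what is tabulated. The only description of the comparison is in Statistical and data analyses, under Feasibility: "A chi-square analysis will determine whether patients in one group versus another estimate their group assignment correctly". The same paragraph says how the result will be used: "patient responses will indicate the rigor of the blinding procedures".

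The Blinding section sets out the data. Patients are asked "whether they believed they received tDCS or sham tDCS, or whether they did not have reason to believe one way or another", which gives three possible answers. The outcome assessors complete a similar questionnaire.

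The article nowhere mentions a table of guess by arm, a comparison of correct guesses with chance, or a blinding index.

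**The concern.** In the stated sentence the outcome is being correct and the contrast is between groups, so the literal table is correct/incorrect by arm. A difference in that table means that one arm guessed right more often than the other. That can happen because patients in both arms favour the same answer, which is compatible with perfect blinding. No difference can mean that both arms guessed right equally often, including always.

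The check carries weight in this trial. Feasibility is part of the first objective, and blinding is one of its two feasibility analyses. The Background and Discussion fault earlier sham conditions as unconvincing and present tDCS as offering a better one. The UEFM is rated by an investigator and the motor activity log is self-reported, so readers will look to the blinding result when they interpret both.

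**Working it through.** The article gives no figure for the blinding test, so there is none to reproduce. The check is how the stated test behaves at the planned size.

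**Inputs**
- Patients per arm: 10, from Sample size estimation ("a sample size of 10 per group would yield 83% power"). Randomization gives 1:1 allocation ("two patients in a block are assigned to PMC tDCS plus CIMT and the other two to the sham tDCS plus CIMT group"), so 20 / 4 = 5 blocks and 5 × 2 = 10 per arm.
- Significance level: two-sided 0.05, an assumption. The article states a level only for the power analysis, in the Figure 2 caption ("The analysis was performed at a 0.05 significance level").
- q_T and q_S: the probability of guessing tDCS in the tDCS and sham arms. The article gives no values, so they are varied as assumptions. Two answers are taken first and the undecided answer is added below.

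**What each table tests.** The correct-guess rate is q_T in the tDCS arm and 1 − q_S in the sham arm. The stated test therefore has the null q_T = 1 − q_S. Blinding means q_T = q_S. The two conditions hold together only at q_T = q_S = 0.5. If both arms are correct with the same probability c, then q_T = c and q_S = 1 − c, which meets the stated test's null whatever c is.

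**Single tables.** Pearson chi-square without correction = N(ad − bc)² / (product of the four margins).
- 9 of 10 correct in each arm. Correct by arm [9,1; 9,1]: ad − bc = 9 − 9 = 0, chi-square 0, p = 1.00. Guess by arm [9,1; 1,9]: 20 × (81 − 1)² / 10,000 = 12.8, p = 0.0003.
- 8 of 10 guess tDCS in each arm. Correct by arm [8,2; 2,8]: 20 × (64 − 4)² / 10,000 = 7.2, p = 0.007 (Yates 0.025, Fisher 0.023). Guess by arm [8,2; 8,2]: chi-square 0, p = 1.00.
- All 20 guess tDCS. Correct by arm [10,0; 0,10]: 20 × 100² / 10,000 = 20, p < 0.0001. Guess by arm shows no difference.

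**Rejection probabilities.** These come from exact enumeration of all 11 × 11 = 121 tables:

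R(p1, p2) = Σ_a Σ_b Bin(a; 10, p1) × Bin(b; 10, p2) × 1[p-value(a, b) ≤ 0.05],

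with a table that has an empty column counted as no rejection. For correct by arm, p1 = q_T and p2 = 1 − q_S. For guess by arm, p1 = q_T and p2 = q_S. Each cell gives Pearson first, then Yates or Fisher (the two agree to the digits shown).

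| Situation | Correct by arm (as stated) | Guess by arm |
|---|---|---|
| Unblinded, 100% correct in both arms | 0% / 0% | 100% / 100% |
| Unblinded, 90% correct in both arms | 0.9% / 0.1% | 98.9% / 95.8% |
| Unblinded, 80% correct in both arms | 3.0% / 0.8% | 80.5% / 63.5% |
| Blinded, q = 0.5 in both arms | 4.2% / 1.3% | 4.2% / 1.3% |
| Blinded, q = 0.6 | 12.9% / 5.4% | 4.0% / 1.3% |
| Blinded, q = 0.7 | 41.8% / 24.3% | 3.7% / 1.2% |
| Blinded, q = 0.8 | 80.5% / 63.5% | 3.0% / 0.8% |
| Blinded, q = 0.9 | 98.9% / 95.8% | 0.9% / 0.1% |
| Blinded, q = 1.0 | 100% / 100% | 0% / 0% |

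A lean towards sham behaves the same way: q = 0.3 gives 41.8% (Pearson), as q = 0.7 does.

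**Undecided answers.** Suppose 20% in each arm are undecided and are scored as not correct, and blinding is perfect. When the remaining guesses lean to tDCS at 0.5, 0.7, 0.8 and 0.9, the stated test rejects 4.0%, 28.0%, 59.0% and 88.4% of the time (Pearson). With 40% undecided the figures are 3.7%, 17.7%, 38.2% and 66.7%. Undecided answers weaken the false signal but do not remove it.

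**The case against.** - **The sentence may be shorthand.** It could stand for a chi-square of guess against assignment, which is a valid test. The Abstract gives no layout, and the Blinding section collects exactly the data such a table needs. The ambiguity is real, but the only sentence that describes the comparison says otherwise, so it needs rewording under either intent.
- **Good blinding is not always flagged.** A reader might infer that the stated test fails any perfectly blinded trial. It does not. With guesses split evenly it rejects 4.2% of the time (Pearson), and at q = 0.6 it rejects 12.9%. Rejection becomes more likely than not only at a lean somewhere between 0.7 and 0.8. A lean to tDCS is plausible because the sham reproduces the initial sensation, but the article does not say how large it would be.
- **There is no pass mark.** The article sets no threshold for blinding and ties no decision to the p-value. That stands, so the rejection rates show how the result would mislead a reader, not a trial decision that would go wrong.
- **Scoring of undecided answers** is detail that an article may leave to a fuller document. That stands too, and the finding does not depend on it.
- **Timing.** Patients are asked only once ("we ask patients at the end of the study whether they believed they received tDCS or sham tDCS"), and a reader might infer that this is an error because improvement can shape the guess. It is an openly stated design choice. An earlier question has its own cost, since it may draw attention to allocation. It is not part of this finding.

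**Conclusion.** The point holds for the test as worded. Its insensitivity to unblinding that is equal in both arms follows from the layout of the table and needs no assumption about how patients lean. At 90% correct in both arms, the stated test rejects about 1% of the time, against about 99% for guess by arm. The opposite error is conditional: it arises when patients in both arms favour the same answer, and rises from about 4% to about 99% as the assumed share guessing tDCS goes from 0.5 to 0.9. These figures rest on 10 per arm, an assumed two-sided 0.05 level, and Pearson without correction. Yates or Fisher lowers them without changing the pattern.

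A reader might go on to infer that the efficacy result is compromised. The article does not support that: the blinding check does not enter the UEFM model, the safety comparison or the sample size. What is at risk is the feasibility conclusion on blinding. Severity: should be fixed.

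**What to change.** Replace the sentence in the Feasibility paragraph with the following:

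- Cross-tabulate the patient's answer (tDCS, sham, undecided) against actual arm and apply an exact test. Cells will be small with 10 per arm, and the article already uses Fisher's exact test for adverse events.
- Report a blinding index for each arm with a 95% CI. One form is Bang's index, (correct − incorrect) / all patients in the arm, with undecided answers kept in the denominator. It separates the cases above: 9 of 10 correct in both arms gives (9 − 1)/10 = +0.8 in each, while 8 of 10 guessing tDCS in both arms gives (8 − 2)/10 = +0.6 for tDCS and (2 − 8)/10 = −0.6 for sham.
- Do the same with the outcome assessors' questionnaire, and state that it is answered for each patient.

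The cost is a change of wording. The patients' three-way answers are already being collected, so no new data or visits are needed.
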